**Methods:**

The study is a single-site randomised controlled trial whereby patients aged ≥65 years who present to the ED of a large Irish hospital will be randomised to the experimental group (ED-based HSCP assessment and intervention) or the control group (usual ED care). The recruitment target is 320 participants. The HSCP team will provide a comprehensive functional assessment as well as interventions to promote a safe discharge for the patient. The primary outcome is ED length of stay (from arrival to discharge). Secondary outcomes include: rates of hospital admissions from the ED, ED re-visits, unplanned hospital admissions and healthcare utilisation at 30 days, and 4 and 6 months of follow-up; patient functional status and quality of life (at baseline and follow-up); patient satisfaction; cost-effectiveness in terms of costs associated with ED-based HSCP compared with usual care; and perceptions on implementation by ED staff members.

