### Outcomes

A range of outcomes will be assessed to identify the potential impact of the intervention on quality, safety, and clinical- and cost-effectiveness of care. The primary outcome of the study is duration of patient ED stay (mean number of hours from time of arrival to discharge or admission). The secondary outcomes include the rates of hospital admissions from the ED (defined as the proportion of patients who are admitted to hospital after their index visits), the duration of hospital admission after the ED index visit, as well as the number of ED re-attendances, nursing home admissions, unplanned hospital visits (and duration of stay) and mortality within 30 days, 4 months and 6 months of the initial index visit. Healthcare utilisation (visits to a general practitioner (GP), public health nurse, home help, private consultation, outpatient department visit, or allied health services) will also be captured at 30 days, 4 months and 6 months after the index visit. Assessment of patient-oriented outcomes include the Barthel Index for Activities of Daily Living [15] as a global measure of function and the EuroQoL’s 5-level of the EQ-5D (EQ-5D-5 L) to measure health-related quality of life [16], which will be conducted at baseline as well as at follow-up (30 days and 6 months, with quality of life also assessed at 4 months).

In addition, patient satisfaction with their index visit will be explored using the 18-item Patient Satisfaction Questionnaire (PSQ-18) [17] at the time of the visit.

An economic analysis will estimate the incremental cost-effectiveness of the HSCP team from the perspective of the Irish public health service, compared with usual care. We will estimate healthcare costs from reference costs from national data sources. Participants’ responses to the EQ-5D-5 L questionnaire will be used to estimate health state utilities using the Irish value set [18], and quality-adjusted life years (QALYs) for each treatment group will be estimated across all time points.

Finally, a process evaluation will be conducted through a mixed quantitative–qualitative design to describe the implementation of the intervention as well as investigate the mechanisms and contextual influences of the implementation as perceived by the HSCP team and representation from the wider ED staff. A detailed study protocol for the process evaluation is available elsewhere [19].

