### Data analysis

Each participant in the study will be assigned a numerical code in order to link data collected at baseline to the data collected at the follow-up at 30 days, 4 and 6 months. Aggregate data will be anonymised. Appropriate descriptive statistics will be used to describe the baseline characteristics of study participants. These will include proportions, percentages, ranges, means and standard deviations, and medians and interquartile ranges (where data are not normally distributed). Differences between the two groups in terms of ED length of stay and hospital length of stay will be analysed using an independent samples *t* test if they meet the assumptions of normality; otherwise, we will employ the nonparametric alternative Wilcoxon Mann–Whitney test with bootstrapping to calculate an effect size 95% confidence interval (CI). The risk of hospital admission rates after the index visit, as well as ED re-visits, unplanned hospital admissions, nursing home admissions and healthcare utilisation at follow-up, will be estimated as odds ratios with 95% CI using a logistic regression, with analyses on follow-up measures adjusted for patient’s age and Identification of Seniors at Risk (ISAR) score at baseline. Patient functioning and quality of life at follow-up will be explored through an analysis of covariance (ANCOVA) adjusting for patient age, baseline ISAR score, baseline Barthel index (for function) and baseline quality of life (for quality of life). Differences in patient satisfaction with their index visit will be analysed using an independent samples *t* test with 95% CI.

For the cost-effectiveness analysis, and as per the Irish Health Information and Quality Authority (HIQA) guidance [20], the primary endpoint of the cost-effectiveness analysis will be costs, QALYs and the incremental cost-effectiveness ratio (ICER). Analysis of uncertainty of the joint distribution of cost and QALYs between the two arms of the study will be presented on a cost-effectiveness acceptability curve to indicate the probability that the HSCP intervention will be cost-effective, based on available trial data and across various willingness-to-pay thresholds.

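### ED re-attendances and unplanned visits are defined as numbers of events but analysed only as logistic odds ratios, with no binary event defined and repeat events unused

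*Protocol article*

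**What the plan says.** The Outcomes section treats two kinds of outcome differently. Hospital admission from the ED is binary, being "defined as the proportion of patients who are admitted to hospital after their index visits". The follow-up outcomes are introduced as "the number of ED re-attendances, nursing home admissions, unplanned hospital visits (and duration of stay", over windows of 30 days, 4 months and 6 months. Healthcare utilisation is described by service, "Healthcare utilisation (visits to a general practitioner (GP), public health nurse, home help" and so on, and is to be captured at the same times.

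The Data analysis section puts all of these into one sentence. It opens with "The risk of hospital admission rates after the index visit, as well as ED re-visits, unplanned hospital admissions" and ends with "nursing home admissions and healthcare utilisation at follow-up, will be estimated as odds ratios with 95% CI using a logistic regression". Analyses of follow-up measures are adjusted for age and baseline ISAR score. The Methods paragraph of the abstract uses a third term for the same outcomes: "rates of hospital admissions from the ED, ED re-visits, unplanned hospital admissions and healthcare utilisation at 30 days".

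**The concern.** Ordinary logistic regression takes a yes/no response. For index admission that response is defined. For re-attendances, unplanned visits and service contacts it is not, and no count or rate model is named. The only workable reading is that each count is reduced to any versus none, and the analyst has to supply that rule.

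The reduction changes what is estimated. A patient who returns four times and one who returns once are scored alike, so an intervention that reduces repeat use without preventing the first return would show no effect. The abstract's Background presents older people as frequent ED users, so repeat use is part of the trial's rationale. For common contacts, most patients in both arms may have at least one, and the binary variable then carries little information.

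This is not a detail left to an analysis plan. The article names a model and an effect measure, and they do not match the outcome it lists.

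**Working it through.** **1. Definition against analysis**

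| Outcome | Outcomes section | Data analysis section |
|---|---|---|
| Index admission | Proportion of patients | Logistic odds ratio: fits |
| ED re-attendances, unplanned hospital visits | Number, by 30 days, 4 and 6 months | Logistic odds ratio: no binary event defined |
| Nursing home admissions | Under the same number wording | Logistic odds ratio: any/none is natural |
| Healthcare utilisation | Visits by service, captured; not expressly a number | Logistic odds ratio: no binary event defined |

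**2. What the article gives for sizing**

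The only calculated figure is the 258 patients for ED length of stay. It reproduces: a two-sided t test with difference 5.58 h, SD 12.49 h and 90% power needs 107 per arm, and 107 × 1.2 = 128.4, so 129 per arm. It has no bearing on these outcomes. No event rate, dispersion or target effect is given for them, so every rate below is an assumption. Two arm sizes are used:
- 129 × 0.8 = 103, the calculated sample less the stated 20% attrition
- (320 / 2) × 0.8 = 128, the recruitment target less the same 20%

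**3. Formulas**

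Counts are negative binomial with means μ0 and μ1 and dispersion k; n is patients per arm; two-sided alpha is 0.05.
- Probability of at least one event: p = 1 − (1 + kμ)^(−1/k)
- Any/none power: Φ[(|p0 − p1| − 1.96·SE0) / SE1], with SE0 pooled and SE1 unpooled
- Count power: Φ[|ln(μ1/μ0)| / SE − 1.96], with SE² = (1/μ0 + 1/μ1 + 2k) / n

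**4. One case in full: 4.0 versus 3.0 contacts, k = 1, n = 103**

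- p0 = 1 − 1/5 = 0.80; p1 = 1 − 1/4 = 0.75.
- SE0 = √(0.775 × 0.225 × 2/103) = 0.0582; SE1 = √((0.16 + 0.1875)/103) = 0.0581.
- Any/none power = Φ[(0.05 − 0.1141)/0.0581] = Φ(−1.10) = 0.135.
- SE² = (0.25 + 0.333 + 2)/103 = 0.0251, so SE = 0.158.
- Count power = Φ(0.288/0.158 − 1.96) = Φ(−0.14) = 0.44.

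**5. Scenarios at 103 per arm**

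The simulation columns are from 400 simulated trials per row.

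| Means, k | Patients with ≥1 event | Any/none, formula | Counts, formula | Any/none, simulated | Counts, simulated |
|---|---|---|---|---|---|
| 4.0 v 3.0, 1 | 80% v 75% | 14% | 44% | 14% | 48% |
| 5.0 v 3.75, 0.5 | 92% v 88% | 15% | 67% | 12% | 60% |
| 1.0 v 0.65, 1 | 50% v 39% | 33% | 54% | 39% | 59% |
| 0.6 v 0.36, 1 | 38% v 26% | 40% | 53% | 41% | 58% |

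**6. Wider range at 128 per arm: true rate ratio 0.70, k from 0.5 to 2**

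| Control mean | Any/none | Counts |
|---|---|---|
| 0.2 | 15–18% | 17–20% |
| 0.5 | 19–30% | 27–39% |
| 1 | 20–39% | 36–59% |
| 3 to 8 | 12–35% | 45–94% |

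Across these cases the same rate ratio of 0.70 appears as an odds ratio anywhere from 0.56 to 0.80, depending on mean and dispersion. The odds ratio is therefore no stand-in for the rate ratio.

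**The case against.** The best defence is that the wording does not force a per-patient count. In the list "the number of ED re-attendances, nursing home admissions, unplanned hospital visits (and duration of stay) and mortality within 30 days", the opening words also run on to mortality, which is binary for each patient, so number of patients with the event is a possible reading. Data analysis speaks of risk, and a logistic model for at least one event answers a risk question validly. That much stands. A reader might infer that the planned analysis cannot answer the trial's question; the document does not support this. The defence does not remove the mismatch, because the same section gives index admission an explicit proportion definition and gives these outcomes none.

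Other stronger readings also fail:

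- **Healthcare contacts as a defined count.** The article says only that visits by service are captured. The largest power losses fall on this outcome, so there the criticism is chiefly one of efficiency.
- **Early deaths scored as no re-attendance.** A reader might fear that this favours an arm with more deaths. Nothing in the article says how deaths are coded; with telephone follow-up they might equally be missing. Mortality is a separate outcome over the same windows.
- **Dates of death already to hand.** Mortality by each time point needs only status, so such dates may not have been recorded.
- **Risk versus odds ratio.** A fall from 50% to 40% is a risk ratio of 0.80 and an odds ratio of (0.4/0.6)/(0.5/0.5) = 0.67. The article states plainly that odds ratios will be reported, so this is loose wording only.

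**Conclusion.** The point holds as a mismatch between definition and analysis for ED re-attendances and unplanned visits, and as an inefficient choice for healthcare contacts. The planned odds ratio gives a coarser answer than the listed outcome calls for and does not estimate a difference in number of events.

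The size depends on rates that the article does not give. On the assumptions above, the loss is negligible for rare events, as might apply at 30 days, moderate for re-visits at means of 0.6 to 1, and large for frequent contacts. It would be wrong to conclude that most power is lost across the board. The outcomes are secondary and the primary analysis is untouched. The change is worth making because it is cheap and because the binary rule would otherwise be chosen by the analyst.

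**What to change.** In the Data analysis section:

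1. Analyse the number of ED re-visits, unplanned admissions and healthcare contacts by negative binomial (or over-dispersed Poisson) regression, adjusted for age and baseline ISAR, reporting rate ratios with 95% CI.
2. Include log time at risk as an offset where dates of death or withdrawal are available. Report mortality alongside, because an offset corrects for shorter exposure but does not remove death as a competing event.
3. Keep logistic regression for index admission and for any nursing home admission.
4. If an any/none analysis is kept for the other outcomes, define it as at least one event by 30 days, 4 months and 6 months, and label it supportive.
5. Use the same term for each outcome throughout, in place of the present mix of number, rate and risk.

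Defining the binary event alone would also remove the contradiction, but it would still leave repeat events unused.

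The cost is revised wording, slightly more analysis work and possibly the recording of dates of death or withdrawal. The Trial status section expects follow-up to run to November 2019, so when the article was submitted in June 2019 this could still be settled before the follow-up data were complete.

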### Power calculation

We estimated our sample size based on our primary outcome (ED length of stay) using G*Power version 3.1. Using data from the Patient Experience Time (PET) database employed in the ED at UHL, the average ED length of stay for patients aged 65 and older for the period 2016–2017 was 13.95 h (standard deviation 12.49 h) [14]. Estimating a 40% decrease in ED length of stay in the intervention group (mean 8.37 h), and with a 20% attrition rate to follow-up, a sample size of 258 patients (129 in each group) is required to achieve 90% power with two-tailed tests at an alpha level of 0.05.

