### Data collection and management

Outcome assessment at baseline and at the end of the visit will be conducted by a research nurse blinded to the patient allocation in order to reduce potential detection bias. A chart review will take place by the research nurse to ascertain demographic details. Outcome assessment at follow-up (30 days, 4 months and 6 months following the index visit) will be conducted via a telephone call.

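### The named ANCOVA for Barthel and EQ-5D-5L ignores intermediate follow-up scores, so the later comparisons lose some precision and can be biased if loss depends on those scores differently by arm

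*Protocol article*

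**What the plan says.** The Outcomes section schedules both scales "at baseline as well as at follow-up (30 days and 6 months, with quality of life also assessed at 4 months"). Barthel therefore has two follow-up scores and EQ-5D-5L has three.

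The Data analysis section gives the method: "Patient functioning and quality of life at follow-up will be explored through an analysis of covariance (ANCOVA"). Its covariates are age, ISAR and the starting value of the scale concerned, so every one is a baseline variable.

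Three other statements bear on missing scores:

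- The Power calculation section sizes the trial "with a 20% attrition rate to follow-up".
- Data collection and management says that follow-up assessment "will be conducted via a telephone call".
- Outcomes also lists "mortality within 30 days, 4 months and 6 months of the initial index visit", so some later scores will be missing because the patient has died.

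The article names no repeated-measures model and no imputation. It does not say that patients with a missing visit are excluded.

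**The concern.** Fitted on its own, an ANCOVA of the 6-month score uses only patients who have that score. It takes nothing from the 30-day score (or, for EQ-5D-5L, the 4-month score) of patients lost later. The comparison then relies on missingness being explained by allocation and the baseline covariates.

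That may fail here. Patients are 65 or older, are reached by telephone, and know their allocation, as the Discussion accepts. Someone doing badly at 30 days may be harder to reach at 6 months, and the strength of that link could differ between arms. The documents make this plausible but do not establish it.

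At stake is the accuracy of the later treatment differences in function and quality of life, when the data needed to protect them are already being collected.

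**Working it through.** **1. Where the 20% comes from.** The plan's control figure for ED length of stay "was 13.95 h (standard deviation 12.49 h"). A 40% decrease is 0.40 × 13.95 = 5.58 h, so d = 5.58 / 12.49 = 0.447. A two-sample t test at 90% power and two-sided 0.05 needs 106.3, so 107 per group. Then 107 × 1.2 = 128.4, rounded up to 129 per group, or 258 in total. This reproduces the plan's figure and shows that the 20% is an input to the length-of-stay calculation. Carried over to the late scores as an assumption, it leaves 0.8 × 320 = 256 patients at the recruitment target, or 0.8 × 258 = 206 at the calculated size.

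**2. Which comparisons are affected.**

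| Comparison | Earlier follow-up score available | Affected |
|---|---|---|
| Barthel, 30 days | none | no |
| Barthel, 6 months | 30 days | yes |
| EQ-5D-5L, 30 days | none | no |
| EQ-5D-5L, 4 months | 30 days | yes |
| EQ-5D-5L, 6 months | 30 days, 4 months | yes |

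**3. Precision under random loss.** Let p be the share missing and r the correlation of the late score with the intermediate score, given baseline. The variance of the likelihood estimate relative to observed-case ANCOVA is about 1 − p·r². Assume correlations of 0.6 with baseline and 0.7 between the two follow-up scores:

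- r = (0.7 − 0.6²) / (1 − 0.6²) = 0.34 / 0.64 = 0.531, so r² = 0.282.
- With p = 0.20 the ratio is 1 − 0.20 × 0.282 = 0.944. Variance is about 6% lower, and the standard error about 3% lower.

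Simulations on the two-visit and three-visit schedules gave 4-7%.

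**4. Bias, one intermediate score (the Barthel schedule).** Large-sample simulation: 400,000 patients per scenario, 20% missing overall, the correlations above, dropout slope of 1 log-odds per SD. Bias in the 6-month difference, in SD units:

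| Loss depends on | ANCOVA, no effect | ANCOVA, 0.3 SD effect | Using 30-day score |
|---|---|---|---|
| baseline, same direction in both arms | 0.000 | 0.004 | within 0.006 |
| baseline, opposite directions by arm | −0.004 | 0.001 | within 0.006 |
| 30-day score, alike in both arms | 0.003 | −0.009 | within 0.006 |
| 30-day score, intervention arm only | 0.061 | 0.058 | within 0.006 |
| 30-day score, opposite directions by arm | 0.122 | 0.124 | within 0.006 |

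In the intervention-arm-only row with a 0.3 SD effect, the arms lost almost equal shares (19.8% and 20.2%). Equal loss rates therefore do not rule the bias out.

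**5. Bias, two intermediate scores (the EQ-5D-5L schedule).** 6,000 simulated trials of 320 patients per scenario, true 6-month effect 0.30 SD, correlations of the 6-month score with the 30-day and 4-month scores of 0.65 and 0.75, 17-20% missing:

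| Loss | ANCOVA | Likelihood | Variance ratio |
|---|---|---|---|
| completely random | 0.302 | 0.302 | 0.935 |
| depends on previous score, alike | 0.287 | 0.301 | 0.959 |
| stronger dependence in control (23% vs 15% lost) | 0.210 | 0.301 | 0.954 |

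The gap is 0.301 − 0.287 = 0.014 SD when loss acts alike and 0.301 − 0.210 = 0.091 SD when it does not. The sign is opposite to step 4 because here it is mainly the control arm that loses its worse patients.

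A further simulation of both schedules, also on assumed inputs, gave 0.01-0.02 SD when loss acted alike and 0.07-0.09 SD when it depended on the earlier score in one arm only.

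**6. Scale.** With 128 scores per arm and a baseline correlation of 0.6, the residual SD is √(1 − 0.36) = 0.8. The standard error is then 0.8 × √(2/128) = 0.10 SD. A bias of 0.06-0.12 SD is 0.6 to 1.2 standard errors; 0.01-0.02 SD is 0.1 to 0.2.

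**The case against.** The strongest reply is that this is a missing-data question rather than a fault of ANCOVA. With complete data, a repeated-measures model with visit-specific baseline adjustment gives essentially the same contrast at each visit. ANCOVA after imputation from the intermediate scores would fit the published wording, and an analysis plan that is not shown may say so. That is fair, and it is why the point is put as what happens if the model is run as written. It remains true that the article commits to a model with baseline covariates only and to no step that would bring in the later scores.

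A reader might infer more than the documents support:

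- *Patients with a missing visit are dropped.* The article does not say so; it is what the named model does on its own.
- *The comparison is biased whenever dropout depends on earlier health.* Baseline health is earlier health and is already adjusted for. Loss that depends on the earlier follow-up score alike in both arms moves the estimate by only 0.01-0.02 SD.
- *20% is the planned loss for these scales.* It is stated within the length-of-stay calculation. That outcome ends at the index visit, so the phrase reads naturally as later loss, but no rate is given by scale or visit.
- *The effect will be understated by 30%.* That is one scenario (0.210 against 0.301) on assumed inputs. Other scenarios overstate the effect.

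The simulations also generate loss from observed scores, so the likelihood analysis is unbiased there by construction. And neither earlier scores nor a mixed model settles what a score means after death.

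**Conclusion.** The point holds as a cheap improvement to two secondary outcomes, not as an error or contradiction in the plan. The named model leaves intermediate scores unused in three comparisons: 6-month Barthel, and 4- and 6-month EQ-5D-5L. The sure cost is small, about 4-7% of variance under random loss. The possible cost is bias, negligible if loss acts alike in both arms and roughly 0.06-0.12 SD or more, in either direction, if its dependence on earlier follow-up scores differs by arm. The size depends on correlations, effects and dropout slopes that the documents do not give. The 30-day comparisons and the primary outcome are untouched.

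**What to change.** For each scale, replace the separate ANCOVAs with one likelihood-based mixed model for repeated measures over all follow-up visits. Terms: allocation, visit, allocation-by-visit, baseline score, baseline-by-visit, age and ISAR, with unstructured within-person covariance. Report the adjusted difference with its 95% CI at each visit. ANCOVA after multiple imputation that includes the intermediate scores serves the same purpose.

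Keep the observed-case ANCOVA as a sensitivity analysis. Report deaths by arm separately and state how scores after death are treated, because the model otherwise extrapolates them implicitly.

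The cost is a change of wording and slightly more programming, with no new data. The analysis relies on a missing-at-random assumption, which is weaker than what the observed-case ANCOVA needs. Trial status puts the end of follow-up after submission of the article, so the change could have been specified before the data were complete.
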